## Abstract

**Background:**

Plantar fasciopathy is the most common reason for complaints of plantar heel pain and one of the most prevalent musculoskeletal conditions with a reported lifetime incidence of 10%. The condition is normally considered self-limiting with persistent symptoms that often last for several months or years. Multiple treatments are available, but no single treatment appears superior to the others. Heavy-slow resistance training and radiofrequency microtenotomy for the treatment of plantar fasciopathy have shown potentially positive effects on short- and long-term outcomes (> 3 months). However, the effect of heavy-slow resistance training compared with a radiofrequency microtenotomy treatment is currently unknown. This trial compares the efficacy of heavy-slow resistance training and radiofrequency microtenotomy treatment with supplemental standardized patient education and heel inserts in improving the Foot Health Status Questionnaire pain score after 6 months in patients with plantar fasciopathy.

**Methods:**

In this randomized superiority trial, we will recruit 70 patients with ultrasound-confirmed plantar fasciopathy and randomly allocate them to one of two groups: (1) heavy-slow resistance training, patient education and a heel insert (*n* = 35), and (2) radiofrequency microtenotomy treatment, patient education and a heel insert (*n* = 35). All participants will be followed for 1 year, with the 6-month follow-up considered the primary endpoint. The primary outcome is the Foot Health Status Questionnaire pain domain score. Secondary outcomes include the remaining three domains of the Foot Health Status Questionnaire, a Global Perceived Effect scale, the physical activity level, and Patient Acceptable Symptom State, which is the point at which participants feel no further need for treatment.

**Discussion:**

By comparing the two treatment options, we should be able to answer if radiofrequency microtenotomy compared with heavy-slow resistance training is superior in patients with plantar fasciopathy.

**Trial registration:**

ClinicalTrials.gov NCT03854682. Prospectively registered on February 26, 2019.

**Supplementary Information:**

The online version contains supplementary material available at 10.1186/s13063-022-06785-w.

## Background

Plantar fasciopathy (PF), formerly labelled as “plantar fasciitis”, is the most common reason for complaints of plantar heel pain and one of the most prevalent musculoskeletal conditions with a reported lifetime incidence of 10% and period prevalence of 3.6–7.0% [1–4].

People with PF report pain during the first steps in the morning or after inactivity which improves with ambulation and worsens during the day [3, 5, 6]. Patients with PF are also prone to greater levels of depression, stress, anxiety, and experience limitations in both mobility and health-related quality of life compared with pain-free individuals [7, 8].

PF has historically been considered a self-limiting condition where 60–80% are expected to achieve symptom-free status within 12 months with conservative treatments [9–11]. This view of PF as a self-limiting condition has been challenged by research [9, 12]. According to a recent cohort study, approximately half of patients referred to a specialized secondary care clinic still experienced pain 10 years after treatment [12]. Furthermore, 40% of patients in a randomized controlled trial still had symptoms 2 years after a treatment protocol consisting of plantar fascia-specific stretching and wearing insoles [9].

### Non-surgical versus surgical treatment

Some of the challenges in achieving a satisfactory recovery after being diagnosed with PF is finding a suitable treatment protocol, where the quality of evidence has been reported to be mostly low or moderate for many of the interventions [13, 14]. The treatment is also reported to be characterized by inconsistent management of the disorder [13–15]. This inconsistency could partly be due to the fact that no single modality treatment seems to be superior to others [14, 16]. According to a recent systematic review by Babatunde et al., none of the investigated treatments (i.e. corticosteroid injection, non-steroidal anti-inflammatory drugs, therapeutic exercise, orthoses, and/or extracorporeal shockwave therapy) was superior to the others [16].

Heavy-slow resistance training (HSRT) was not included in the above-mentioned systematic review, but it is generally known for significant efficacy in the rehabilitation of lower-limb tendinopathies [17–20]. Rathleff et al. reported a greater reduction in self-reported pain after 3 months of plantar-specific strength training and insoles compared with traditional treatment with plantar-specific stretching and insoles for PF patients [20]. HRST has also shown better micro-structural improvements in tendon tissue and pain reduction compared to traditional eccentric training of the patella and Achilles tendon [17, 18].

HSRT, as a form of treatment for all types of chronic injuries, has potentially gained ground because the training is easy to perform for the patient and has shown good clinical applicability for the healthcare staff. This is despite the fact that the effects of HSRT for patients with PF have only been compared to stretching, and the only other research in the area has compared different exercise protocols of the same exercise [20, 21].

Traditionally, surgical treatment for PF is considered as a last resort but could alternatively be considered as a treatment option between 6 and 12 months from symptom onset [22–24]. A newer minimally invasive treatment modality known as radiofrequency microtenotomy (RFM) for the treatment of PF has shown promising results in short- and long-term results. The treatment consists of a probe which is passed down through the skin to the tendon where radio waves are discharged into the tendon’s affected area through independent inserts. This excites and heats the soft tissue to relatively low temperatures (40–70 °C). The heating and the radio waves are believed to create a renewed inflammatory response, as well as positively affect the local tissue’s growth factors and nociceptors [25, 26]. The treatment is gentle, and several non-randomized studies have shown good results and minimal complications in the treatment [25–29]. RFM treatment is reportedly as effective as the more extensive and invasive surgery, open plantar fasciotomy. Moreover, a faster return to normal activities, fewer complications, and reduced pain are seen with RFM treatment compared to open plantar fasciotomy [28–32].

To date, RFM has not yet been compared to other types of conservative treatments including HRST. By comparing HSRT with RFM treatment, we should be able to answer if RFM is superior to performing exercises.

## Objectives and hypothesis

The purpose of this trial is to investigate the efficacy of HRST versus RFM by comparing patients’ pain levels with the Danish version of the Foot Health Status Questionnaire (FHSQ-DK) 6 months after treatment initiation. Both groups will in addition receive standardized patient education and a heel insert. Our hypothesis is that surgical treatment is better than non-surgical treatment measured on the FHSQ-DK (pain) score after 6 months.

## Methods

### Design

A prospective randomized clinical superiority trial is performed with a balanced randomization (1,1). Reporting of the protocol follows the Standard Protocol Items: Recommendations for Interventional Trials (SPIRIT) statement [33] (checklist uploaded as Additional file 1). Before the inclusion of the first participant, the trial was registered at ClinicalTrials.gov (NCT03854682).

### Participants and recruitment

Individuals referred to the Department of Orthopaedic Surgery and Traumatology, Kolding, Lillebaelt Hospital in Denmark, with plantar heel pain will be examined and screened for potential participation. The recruitment will be performed in a standard outpatient clinic setting by a specially trained healthcare personnel (SM), who has a special interest in PF pathology. The recruiting healthcare personnel is also trained and experienced in ultrasound scanning of the plantar fascia thickness with regard to the diagnostic evaluation.

Participants will attend the baseline, and a link to the questionnaires used will be sent via REDCap (Vanderbilt University, Nashville, TN, USA) to participants’ e-mail addresses for the 4-week, 12-week, 26-week, and 52-week follow-ups.

### Eligibility criteria

The diagnosis of PF is based on the diagnostic criteria according to the literature [5, 6, 21]: pain must be well-defined with the initiation of pain after rest (first-step pain), and the gait pattern should be changed to relieve the foot. Palpation is performed to identify the area of pain, which should be located at the proximal plantar fascia insertion area, and the patient is examined for differential diagnoses (e.g. Tinel’s sign over the tarsal tunnel, fat pad syndrome, anamnesis of bilateral debut of symptoms). Findings are verified with ultrasound, where a plantar fascia thickness of > 4 mm should be present.

Patients diagnosed with PF, who are older than 18 years; have well-defined plantar heel pain, a pain intensity of 30/100 within the last 7 days (VAS), and palpation tenderness at the plantar fascia insertion; and experience initiation pain after rest (first-step pain), are offered participation in the study. The duration of symptoms must be over 9 months. People with systemic diseases, diabetes, previous heel surgery, and Tinel’s signs over the Tarsal tunnel; pregnant women; and people who have received medical or physiotherapy treatment/cortisone injection within the last 3 months or have a fascia thickening (< 4 mm) are excluded (see Table 1 for the in- and exclusion criteria).

**Table 1 Tab1:** Inclusion and exclusion criteria

Inclusion	Exclusion
≥ 18 years	History of systemic diseases and neuropathy
Well-defined plantar heel pain	Diabetes
VAS ≥ 30/100 within the last 7 days	Pregnant
Palpation tenderness at the plantar fascia insertion	Previous heel surgery
First-step pain	Tinel’s signs over the tarsal tunnel
Duration of symptoms ≥ 9 months	Received medical/physical therapy treatment and/or cortisone injection within the last 3 months
	Fascia thickening (< 4 mm)

Patients are informed orally and in writing, and if they are willing to participate, they will sign a declaration of consent before inclusion. After this, randomization will take place. Patients who want a consideration period will be given a statement of consent and “subjects’ rights” and will be contacted by telephone after 3 days.

All patients are informed about the latest knowledge within the area of PF, including the expected prognosis, as well as risks. They will also receive information about the trial’s content, purpose, and time horizon, including a right to withdraw their consent at any time.

It is permitted that patients who have performed self-administered treatment in the form of foot massage, thermotherapy, and stretching of the fascia may continue with this, provided this has been done for a minimum of 4 weeks before inclusion.

### Randomization

Shortly after the written consent is signed, the patient will be contacted by a research secretary for further allocation. The randomization is performed by a research secretary with a software program (REDCap), which generates the allocation sequence in blocks of 10 patients, where 5 will be randomized to HRST treatment and 5 will be randomized to RFM treatment. The randomization within the blocks of 10 is random and is done without stratification. The randomization is done by the secretary in a separate room before contact.

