### Blinding

The nature of the trial means that the group allocation cannot be hidden (blinded) from the patient or the researchers involved. To reduce the risk of bias, the assessor and statistician are blinded, and patients are encouraged not to state their assigned treatment in case of contact.

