### Trial status

Recruitment was started on February 7, 2020, and the first participant was included on the same date. One amendment has been made to the local ethics committee and has been approved (version 3.5, March, 2022). The amendment concerns a change of the responsible person for the research project from being CJ to AS, a prolonged research period to 1.7. 2025, and a change in the randomization method performed in REDCap. When this protocol was submitted for publication, a total of 31/70 (54 screened) participants had been included in the trial. We expect recruitment to be completed by July 2024.

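### A single published block size of 10 in an open, one-department trial makes block ends foreseeable to anyone who tracks past assignments; randomly varied blocks would remove nearly all certain allocations

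*Protocol article*

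**What the plan says.** The Randomization section of the protocol article states that the REDCap program "generates the allocation sequence in blocks of 10 patients", "where 5 will be randomized to HRST treatment and 5 will be randomized to RFM treatment". It adds: "The randomization within the blocks of 10 is random and is done without stratification". No second block size or random variation of size is mentioned.

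On concealment, the same section says: "Shortly after the written consent is signed, the patient will be contacted by a research secretary for further allocation", and "The randomization is done by the secretary in a separate room before contact".

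The Blinding section says that "group allocation cannot be hidden (blinded) from the patient or the researchers involved"; only the assessor and the statistician are blinded. Participants and recruitment describes one hospital department and one specially trained member of staff who recruits. Under Eligibility criteria, patients who want time to consider "will be contacted by telephone after 3 days".

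Trial status reports that, at submission, "a total of 31/70 (54 screened) participants had been included in the trial". It also reports an approved amendment that changed the randomization method in REDCap, without details.

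**The concern.** With a constant 5:5 block, the remaining allocations in a block are fixed once one arm has used its five places. An observer needs the block size, the past assignments and the block starts. The size is published. Past assignments are plausibly known to the team because treatment is open. There are no strata or further sites to split the count, so there is one sequence to follow.

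Allocating after consent, in a separate room, hides the current assignment. It does not prevent someone from inferring the next one from those already made, and that inference can be drawn before consent. At that stage the recruiter is still judging palpation tenderness and a fascia thickness near 4 mm, and informing the patient. The consideration period leaves some room to shift the timing of entry.

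What is at stake is selective enrolment or deferral according to the expected arm. The stated hypothesis favours surgery, and the primary outcome is reported by patients who know their treatment, so selection at entry would add to an existing vulnerability.

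**Working it through.** The article gives no figure for predictability, so there is none to reproduce.

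**Inputs.** Block of 10, split 5:5, no strata (Randomization); 70 planned and 31 included at submission (Trial status). Hence 70/10 = 7 full blocks and 70 − 31 = 39 participants remaining at submission.

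**Certain allocations per block.** The last k places are all certain when they all belong to one arm:

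P(k) = 2·C(10 − k, 5)/C(10, 5), with C(10, 5) = 252.

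| k | Calculation | Probability |
|---|---|---|
| 1 | 252/252 | 100% |
| 2 | 112/252 | 44.4% |
| 3 | 42/252 | 16.7% |
| 4 | 12/252 | 4.8% |
| 5 | 2/252 | 0.8% |

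The expected number is the sum: 420/252 = 1.67 per block, or 16.7%. The closed form 2m/(m + 1) with m = 5 gives the same, 10/6 = 1.67. Over 7 blocks that is 7 × 1.67 = 11.7 of 70.

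**Average guess rate.** Always guessing the arm with more places left is right 5 + (1024/252 − 1)/2 = 6.53 times in 10, or 65.3%, against 50% by chance.

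**The 39 remaining at submission.** The answer depends on where the current block began.
- Blocks unbroken from participant 1: participant 31 took the first place of block 4, so 9 places of that block and 3 full blocks remain. A first place is never certain, so the expected number is 4 × 1.67 = 6.7 of 39 (17.1%).
- New block at participant 32: 3 full blocks and the first 9 places of a fourth. The tenth place, always certain, falls outside, so the expected number is 3 × 1.67 + (1.67 − 1) = 5.7 of 39 (14.5%).

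**Randomly varied sizes.** These were simulated for an observer who knows the set of sizes and all past assignments, but not the order of the sizes. The ranges cover sequences of 39 and 70.

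| Block sizes | Certain allocations | Average guess rate |
|---|---|---|
| Fixed 10 | about 15–17% | about 64–65% |
| 4, 6, 8 | about 2.3% | about 67–68% |
| 6, 8, 10 | about 1.6–1.8% | about 66% |
| 8, 10, 12 | about 1.4–1.6% | about 64–65% |

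All three mixtures remove most of the certainty. Of the three, only 8, 10 and 12 does so without raising the guess rate, because its average size is no smaller than the present one.

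**The case against.** The case for leaving the scheme alone is substantial.

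- **Ten is not a small block for 70 participants.** Among fixed sizes it is less predictable than 8, 6 or 4, where certain allocations are 20%, 25% and 33%. This stands, and it limits the size of the problem.
- **Tracking is not documented.** The Blinding section makes it plausible that the recruiter learns assignments, but does not say so. A secretary performs the allocation and the contact that follows, and patients are encouraged not to state their treatment. This stands: the point is conditional.
- **Block starts are unknown.** The amendment changed the randomization method without saying how, so the article does not show whether blocks of 10 ran from the first participant. This stands, and is why a range is given.
- **Analysis gives some protection.** The primary model includes baseline pain constrained to be equal between groups. That adjusts for selection on baseline pain, but not for selection on unmeasured prognosis.
- **Doing without strata is ordinary at this sample size.** It matters here only because it leaves one sequence to follow.

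A reader might infer that upcoming allocations in general can be predicted. The document does not support that: only about one in six is certain, and guessing overall is right about 65% of the time. A reader might also take 39 as the number still to enrol once the block size was public. It is the count at submission; the count at publication is not given.

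**Conclusion.** The point holds in a limited form. A constant, published block of 10 in an open trial with one department and one recruiter makes block ends foreseeable, and allocation by a secretary in a separate room does not prevent that. The size is 1.67 certain allocations per block (16.7%), or about 5.7 to 6.7 of the 39 remaining at submission.

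This assumes that the observer knows the past assignments and the block starts, neither of which the article states. Nothing shows that selective enrolment has taken place, and the sample size is not affected. It is a weakness worth closing because closing it is cheap, not an error or contradiction in the text.

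**What to change.** For participants not yet enrolled, load a new REDCap allocation table with block sizes that vary at random and are no smaller on average than now, for example 8, 10 and 12 in random order. Someone outside recruitment should generate it, and the sizes should stay out of documents available to the site until enrolment closes.

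Certain allocations would fall from about 15–17% to about 1.6%, even if the set of sizes became known (1.6% of 39 is about 0.6 participants). The average guess rate would stay at about 64–65%. Blocks of 4, 6 and 8 are not advised: they also remove most of the certainty, but raise the guess rate to about 67–68%. That strategy needs only the running imbalance, so keeping the sizes secret does not stop it.

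The cost is a new allocation table, a short amendment (the randomization method has been amended once already) and a possible final imbalance of a few participants. If enrolment has closed, the change no longer applies.

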### Blinding

The nature of the trial means that the group allocation cannot be hidden (blinded) from the patient or the researchers involved. To reduce the risk of bias, the assessor and statistician are blinded, and patients are encouraged not to state their assigned treatment in case of contact.

### Sample size

Based on a standard deviation of 19.7 points, a two-sided significance level of 0.05, and a power of 80%, it will require 32 participants in each group to be able to detect a difference in the clinically relevant 14.1 points in the pain domain of FHSQ-DK [34]. To account for possible drop-outs, we will include a total of 70 participants.

### Pilot study

Prior to the study, a pilot study was made in which the patients’ preference (*n* = 24) for treatment type (due to patients’ equipoise) [35] was compared to symptom duration and previous treatment. Patients were presented with a short, standardized text and video of the two types of intervention and asked if they would choose the non-surgical or surgical treatment. No significant preference was found compared to the duration of symptoms or prior treatment.

### Statistical analyses

All statistical analyses have been planned in cooperation with a statistician assigned to the statistical department of OPEN (Odense, Denmark) that are responsible for data storage in REDCap. The primary analysis will investigate the between-group difference in FHSQ-DK pain. The analyses will be performed by a blinded data analyst (at the group level) using a linear mixed effect model with the participant as a random effect and time (baseline, 4, 12, 26 and 52 weeks) and group allocation (HRST or RFM) as fixed effects. The model will include the baseline measurements with the constraint of no group difference at baseline.

An intention-to-treat analysis is planned, where a per-protocol analysis could be carried out (as a supplementary analysis), provided that a very varying following is seen with the intervention procedures. Missing outcome data will be imputed using a multivariate model based on a normal distribution.

It is also planned that analyses of the mean values of the secondary continuous outcomes will be done by using linear mixed models. Resample bootstrap will be used in case there are substantial ambiguous data for these outcomes.

The time when PASS is obtained between the two groups is compared. If a participant changes PASS multiple times (e.g. achieving PASS before 12 weeks, reporting not to have achieved PASS at 26 weeks, and then having achieved PASS again at the 52-week follow-up), only time to the first PASS achieved is used in the analysis [36]. We will calculate the relative risk of achieving PASS at each follow-up.

In an additional analysis, we will by linear mixed models investigate if anthropometric baseline values, e.g. gender, age, and length of symptoms influence the primary outcome.

Dropouts will be registered, and the reasons for this will be noted.

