#### Primary outcome

The primary outcome is the mean pain domain score of the FHSQ-DK after 6 months [44].

FHSQ-DK consists of 13 questions that are divided into four domains: pain, function, footwear, and general foot health. It takes the patient less than 10 min to complete. FHSQ scores for each domain range from 0 (worst) to 100 (best). The minimal clinically important difference in the pain domain is reported to be 14.1 points, 7.4 points for function, and 9.2 points for footwear [34]. FHSQ-DK is a Danish validated translation of the original questionnaire [44]. FHSQ has been reported as the preferred questionnaire for patients with plantar fasciopathy [45].

The selected HRST regimen has shown a larger pain reduction after 3 months, but not after 12 months compared to a stretching group [20], and the HRST regimen may not be sufficient to achieve Patient Acceptable Symptom State in most people with plantar fasciopathy after 12 weeks [21]. It can take time to manifest changes to a training regimen, and therefore, we aimed for a primary end-point at 6 months.

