### Perspective

Patients ask for both short-term and long-term pain reduction, where RFM and HRST may potentially offer this based on different adaptive mechanisms and possibly different temporal profiles. Despite our hypothesis that RFM treatment will be superior at 6 months (FHSQ-DK pain), the effects of HSRT could potentially be similar, which potentially would have a clinical impact on future indications for RFM treatment. There are obvious differences between the chosen treatments in the required time, personnel, costs, and materials. The treatment offered in the HRST group requires the least resources, whereas the RFM group requires the most resources in material, personnel, and specialized education. However, this difference may be equalized by the potential savings on a societal level in terms of reduced sick leave or on a personal level in terms of health-related improvement and personal expenses. Any future implementation will also be dependent on the patients’ experiences and the final results of the study.

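### The terms listed for the primary mixed model (time and group) do not yield the 6-month difference, conflict with the stated baseline constraint, and come with no named 26-week contrast

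*Protocol article*

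**What the plan says.** The target is a single visit. The Primary outcome section states: "The primary outcome is the mean pain domain score of the FHSQ-DK after 6 months". Objectives and hypothesis places the expected superiority of surgery at 6 months, and Outcomes/variables names 6 months as the primary end-point. Sample size plans for "a difference in the clinically relevant 14.1 points in the pain domain of FHSQ-DK" and concludes that "it will require 32 participants in each group", with SD 19.7, 80% power and "a two-sided significance level of 0.05".

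Statistical analyses describes the primary model as a linear mixed model with participant as random effect and "time (baseline, 4, 12, 26 and 52 weeks) and group allocation (HRST or RFM) as fixed effects". It then adds: "The model will include the baseline measurements with the constraint of no group difference at baseline". The quantity of interest is described only as the between-group difference in FHSQ-DK pain, with no visit attached. In the same section the PASS analysis does get its timing: a relative risk at every follow-up.

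Under Perspective, the article allows that the two treatments may act with "possibly different temporal profiles".

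**The concern.** In a model with time and group as main effects, there is one group coefficient and it is the same at every visit. It equals the 6-month difference only if the effect is constant over the visits that are pooled. Baseline is one of the five listed time levels, and no effect can exist there, so even a constant treatment effect would be diluted under the plain reading.

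The constraint sentence does not settle the matter. It shows that the group effect must differ between baseline and follow-up, so some term beyond the two listed is needed. It does not say whether that is one common follow-up effect or a separate effect at each visit.

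At stake is the primary result. If the effect builds up late, a pooled coefficient understates the 6-month benefit. If the effect comes early and then disappears, a pooled coefficient can be reported as 6-month superiority when there is none. The same wording would carry over to the other FHSQ domains, for which linear mixed models are also planned.

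**Working it through.** **1. Reproduce the plan's sample size.** Inputs from Sample size: δ = 14.1, σ = 19.7, two-sided α = 0.05, power 80%. Normal approximation: n = 2(1.96 + 0.8416)²σ²/δ² = 2 × 7.849 × 388.09 / 198.81 = 30.6, so 31 per arm. The two-sample t-test gives 31.63, so 32 per arm, which matches the plan (power 80.5% at 32). The stated n is therefore that of a comparison at one time point.

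**2. Three readings of the model.**
- A: time plus a plain group main effect. One coefficient covers five visits. Setting it to zero at baseline sets it to zero everywhere, so the stated constraint cannot hold.
- B: time plus one common group effect at the four post-baseline visits. The constraint holds; the effect is pooled over weeks 4 to 52.
- C: time plus a separate group effect at each post-baseline visit (constrained longitudinal model). The constraint holds, and the 26-week difference is one of the coefficients.

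**3. Assumptions for the illustration.** From the plan: σ = 19.7 (applied to every visit) and n = 32 per arm. Assumed: complete data, known variance, and equal correlation ρ between visits, which is what a single participant random effect with independent residuals implies. The main value is ρ = 0.5, with 0.3 and 0.7 as the range. The effect profiles are also assumed, because the article gives none.

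**4. Formulas.** With equal correlation, A and B weight their visits equally, so each expected estimate is a simple mean of the visit effects. Let K = 2σ²/n = 2 × 388.09 / 32 = 24.26. At ρ = 0.5:
- A: SE² = K(1 + 4ρ)/5 = 24.26 × 0.600, SE = 3.81
- B: SE² = K[(1 + 3ρ)/4 − ρ²] = 24.26 × 0.375, SE = 3.02
- C: SE² = K(1 − ρ²) = 24.26 × 0.750, SE = 4.27

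Rejection probability = Φ(|estimate|/SE − 1.96) + Φ(−|estimate|/SE − 1.96).

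**5. Results at ρ = 0.5** (estimate, rejection probability):

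| Effects at weeks 4, 12, 26, 52 | A | B | C, week 26 |
|---|---|---|---|
| 14.1, 14.1, 14.1, 14.1 | 11.28, 84% | 14.1, above 99% | 14.1, 91% |
| 0, 7.05, 14.1, 14.1 | 7.05, 46% | 8.81, 83% | 14.1, 91% |
| 0, 7.05, 14.1, 7.05 | 5.64, 32% | 7.05, 65% | 14.1, 91% |
| 14.1, 14.1, 0, 0 | 5.64, 32% | 7.05, 65% | 0, 5% |

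Examples. Row 1, A: 4 × 14.1 / 5 = 11.28. Row 2, B: (0 + 7.05 + 14.1 + 14.1)/4 = 8.81. Row 4, B: (14.1 + 14.1 + 0 + 0)/4 = 7.05; 7.05/3.02 = 2.34, and Φ(2.34 − 1.96) is about 0.65.

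**6. Sensitivity to ρ.** In row 4 the rejection rate under B is 64%, 65% and 77% at ρ = 0.3, 0.5 and 0.7. The power of C at week 26 for a true 14.1 is 85%, 91% and 98%, above the planned 80% throughout.

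**The case against.** The strongest reply is that the constraint sentence already rules out a plain main-effects model. No group difference at baseline, with baseline kept as an outcome level, is the usual description of a constrained longitudinal model, whose standard form has visit-specific effects. The 6-month target is fixed in several places, so the between-group difference can naturally be read as the one at 6 months. An article condenses its full plan, and the fuller plan may name the interaction and the contrast.

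Much of this stands. A reader might infer that the trial will in fact estimate an effect averaged over weeks 4 to 52. The article does not support that as a fact: it is reading B only, and reading C is at least as compatible with the constraint. A reader might also infer that the protocol contradicts a constant effect. It does not: Perspective says only that the profiles possibly differ, and no section gives an expected time course for the difference between surgery and training. The Primary outcome section reports that training beat stretching at 3 months but not at 12. That comparison is against stretching, and it does not show that the training effect itself fades.

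What does not stand is the claim that this is mere condensation. The section does not leave the model open. It lists the terms, and those terms can be squared with neither the constraint in the next sentence nor the 6-month end-point unless the reader adds something that is not listed.

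**Conclusion.** The point holds as a defect in the stated model: the listed fixed effects are inconsistent with the baseline constraint and are not tied to the 6-month end-point. It is not proof that the wrong quantity will be estimated, since the authors may intend visit-specific effects.

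The size depends on which reading is implemented and on how the effect varies over time. If the effect is constant after baseline, the common post-baseline model is unbiased (14.1) and only the plain main-effects model is off (11.28). If the effect varies, both pooled models miss the 6-month value: 8.8 or 7.05 instead of 14.1 under the late profile, and about 65% (common post-baseline effect) or 32% (plain main effect) false claims of a 6-month difference under the early-only profile, at ρ = 0.5. The profiles and correlations are assumptions chosen to show the mechanism; they do not predict this trial's data.

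Because following the text literally can change the primary conclusion, the wording should be settled before the analysis.

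**What to change.** Replace the model sentence with wording such as: fixed effects are time (categorical: baseline, 4, 12, 26 and 52 weeks) and group-by-time at the four post-baseline visits, with no group effect at baseline; the single primary estimate and test is the group difference in FHSQ-DK pain at 26 weeks, with its 95% confidence interval; the 4-, 12- and 52-week differences are secondary. Use the same form for the other FHSQ domains. If the statistical analysis plan already says this, a consistency note is enough.

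The cost is one sentence. No extra patients or data are needed, and the sample size stays as planned, since the 26-week contrast has about 85% to 98% power at 32 per arm over the assumed correlations. Trial status reports 31 of 70 participants included at submission. The change should be dated and made before the analyst sees outcome data by group.
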